## Abstract

**Background:**

Maternal smoking is a key cause of poor outcomes for mothers, babies and children and Wales has higher rates of smoking in pregnancy than any other UK country. Despite various improvements within the NHS Stop Smoking Service to strengthen the intervention for pregnant women, referrals and successful quit attempts for this group have continued to remain extremely low. A key element of UK national guidance for smoking cessation during pregnancy is to provide a flexible and tailored service to help increase levels of engagement. This study aims to test the effectiveness of three different models of service delivery to address the gap in the evidence base about how to deliver a flexible, tailored smoking cessation service to pregnant women.

**Methods:**

This study will adopt a quasi-experimental design over a 12 month period. The setting is four of Wales’ seven Health Boards using an integrated approach between maternity services, local public health teams and the NHS Stop Smoking Service. Core recommendations from UK public health guidance are being implemented across intervention and usual care sites. Stop smoking support for pregnant women in intervention sites is being delivered more flexibly than in usual care sites. Both qualitative and quantitative approaches will be adopted to capture important contextual information and consider multiple perspectives. A health economic analysis will be undertaken using a cost-consequences analysis approach. The primary outcome measure is engagement with stop smoking services (defined as having at least one face-to-face therapeutic contact with a clinician).

**Discussion:**

Supporting pregnant women to stop smoking is a challenging area of public health. The proposed study will address several areas where there are key evidence gaps relating to smoking cessation interventions for pregnant women. Specifically, how best to encourage pregnant women to attend a specialist stop smoking support service, how to deliver the service and who should provide it.

**Electronic supplementary material:**

The online version of this article (doi:10.1186/1471-2458-14-1041) contains supplementary material, which is available to authorized users.

## Background

A third of pregnant women living in Wales smoke before or during their pregnancy compared to just over a quarter of women living in other areas of the UK [1]. This is a major concern since maternal smoking is a key cause of poor outcomes for mothers, babies and children. It is associated with increased risk of miscarriage, perinatal death, prematurity, low birth weight and congenital abnormalities in the baby in particular of the heart, face and limbs [2, 3]. Supporting pregnant women to stop smoking is thus an important area of public health.

High quality evidence exists for interventions to promote smoking cessation in pregnancy. A Cochrane review found that psychosocial interventions led to a reduction in smoking during pregnancy and reduced the risk of low birth weight and pre-term birth [4]. UK public health guidance on interventions aimed at stopping smoking in pregnancy and following childbirth provides a clear pathway and referral mechanism for pregnant smokers into NHS Stop Smoking Services [5].

A key component of this guidance is carbon monoxide (CO) testing for all pregnant women to assess their level of exposure to CO either as smokers themselves or from other sources. Test results are used to ensure the appropriate identification of smokers for onward referral to specialist support services. It has been estimated that 20 per cent of smokers deny their habit when cotinine measurements are compared with self-report [6], leaving these pregnant smokers without the information available to facilitate a quit attempt. It has been reported in UK based research that employing the carbon monoxide test in conjunction with self-report improves the identification of smokers, but that maternity staff have found it difficult to discuss smoking and administer the test [7].

A further key element of UK national guidance for smoking cessation during pregnancy is to provide a flexible and tailored service for pregnant women to help increase levels of engagement. This is due to the fact that pregnant women may not feel comfortable or have all their needs met when attending generic services. Many English stop smoking services offer a flexible service for pregnant women [8]. However, it is not known how best to deliver such a service or who should provide it.

Within the Welsh NHS Stop Smoking Service^a^, various service improvements have occurred since 2009 with a view to strengthening the referral system for pregnant women who smoke from antenatal units to the stop smoking service. These service improvements have included additional training of midwifery staff, in line with National Institute for Health and Care Excellence (NICE) guidance, to encourage the use of CO testing. Despite this, referrals into the service and engagement with pregnant women has continued to remain extremely low. For example, data from the Stop Smoking Service show that in the referral period May 2012-March 2013, 1,817 pregnant smokers were referred to the service from maternity services, but only 529 went on to accept an appointment. At this time, there were around 32,000 births in Wales [9] based on a smoking prevalence of 33% [1], 5.6% of smokers were referred to the service, and 1.6% of smokers accepted an appointment. In response, key partners were brought together across Wales to develop a public health study, Models for Access to Maternal Smoking cessation Support (MAMSS) with the aim of testing the effectiveness of three different models of service delivery to address the gap in the evidence base about how to deliver a flexible tailored smoking cessation service to pregnant women.

## Methods

This study will be undertaken as a quasi-experimental design. Donabedian’s conceptual model for examining health services and evaluating quality of care as a framework for examining structures, processes and outcomes will be applied [10]. The setting will be four of Wales’ seven Health Boards. These are single local health organisations responsible for planning, securing and delivering all healthcare services within a geographical area. The Health Boards involved in the study are self-selected and are geographically diverse. Total population figures range from 294,497 to 690,434 [11] and live births range from 63.9 to 66.3 per 1000 women aged 15-44 [9] (see Table 1).

**Table 1 Tab1:** **Total population and live births per 1000 for Health Boards participating in MAMSS**

Health board	Total population [11]	Live births per 1000 women aged 15-44 [9]
Health board 1	519,781	60.0
Health board 2	577,981	61.8
Health board 3	690,704	64.8
Health board 4	294,497	61.7

### Interventions

The study will take place over 12 months using an integrated approach between maternity services, local public health teams and the NHS Stop Smoking Service. In each Health Board, an intervention and a usual care site will be selected from existing community midwifery teams. Sites will be selected on the basis of high rates of pregnant smokers, and a similar demographic profile in intervention and usual care sites within each Health Board. Pregnant smokers (i.e. those who are self-reported current smokers or have a CO reading # 7 ppm^b,^^c^ or who have quit in the two weeks prior to their booking appointment [5]) will be referred to the intervention or usual care NHS Stop Smoking Service on an opt out basis (see Figures 1 and 2). This automatically refers pregnant smokers to the service. The two main points for referral are the first antenatal appointment (at home or in a community antenatal clinic by the midwife) or subsequent scheduled antenatal care visits (by the midwife). However, the referral process can take place at any stage during pregnancy, for example, during the postpartum period whilst under the care of a midwife.

**Figure 1 Fig1:**
[figure not shown]
**Referral and treatment in usual care and intervention sites.**

**Figure 2 Fig2:**
[figure not shown]
**Recruitment flow diagram.**

In intervention sites, pregnant smokers will be referred to one of three different models of service delivery where smoking cessation services are provided by maternity support workers, midwives or smoking cessation advisors dedicated to working with pregnant women, all offering a flexible service designed to meet the needs of the women. The core elements of the evidence base to be implemented in all intervention sites will include:

 Strict adherence to NICE opt out smoking cessation pathway for pregnant women, including CO monitoring. Smoking cessation services being more closely aligned to maternity services (provided as part of the package of maternity care). Referral from midwife to smoking cessation support within 48 hours Flexibility in service model with a women centred approach.

Each intervention site will recruit a whole-time equivalent (WTE) maternity support worker (employed by the Health Board), midwife (employed by the Health Board) or dedicated Stop Smoking Advisor for pregnant women (employed by the NHS Stop Smoking Service) who will deliver stop smoking support to pregnant women. These staff will receive referrals directly from midwives to provide an intensive smoking cessation intervention at times and settings of the women’s choice, including home visits. During every subsequent antenatal appointment, women will be asked about their smoking status and referred as appropriate. If a woman has declined treatment (i.e. she opts-out by not answering the telephone to stop smoking services or refuses an assessment appointment) she will be asked if she would like to be re-referred during each follow-up appointment.

Clients in intervention sites will be offered smoking cessation support for the duration of their pregnancy if required. The support they receive will follow an adapted behavioural intervention model documented in the NHS Stop Smoking Service delivery manual, which is based on withdrawal oriented therapy (Maudsley model) [12]. This may involve a combination of telephone and face to face support as well as motivational support by email and or text, dependent upon the needs of the client (see Figure 1). A detailed manual for specialist smoking cessation staff has been developed for use in all intervention sites detailing the referral pathway, intervention programme, policies, procedures and support materials.

### Comparison group (usual care)

Pregnant smokers will be referred on an opt out basis to NHS Stop Smoking Services in usual care sites. The core elements of this service are:

 Referrals received by NHS Stop Smoking Service from midwives via fax or phone call. Stop smoking staff make an attempt to contact the pregnant women within 48 hours to discuss benefits of quitting, offer support and arrange an assessment session. NHS Stop Smoking Service staff attempt to contact the client by telephone twice more if contact has not been established, and send a follow up letter if no response. Clients who do not opt out are fast tracked into a one-to-one assessment session appointment within 48 hours. Assessment sessions are conducted in community venues. Women are offered six further sessions of intensive behavioural support in community venues or by telephone. If the client requires additional support following the seven sessions, the advisor will arrange to make contact by telephone in two weeks to provide an additional follow up.

### Outcome measures

The primary outcome measure is engagement with stop smoking services (defined as having at least one face-to-face therapeutic contact with an advisor) and secondary outcome measures are pregnant smokers who set a quit date; pregnant smokers who quit at four weeks follow-up (CO verified); smoking status at the time of birth or third trimester and 52 weeks; and birth outcomes (low birth weight (<2500 g), preterm birth <37 weeks).

Process measures will assess fidelity to protocols, feasibility, acceptability, maintenance and sustainability should the interventions be rolled out on a wider scale. Data will be obtained from available data sources within maternity services and the NHS Stop Smoking Service on specific aspects of the referral pathway and treatment programme.

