### Sample

Women who are pregnant and smoke or who have quit smoking in the two weeks prior to their initial antenatal booking appointment will be eligible to participate. The inclusion criteria are pregnant or postnatal women, under the care of a midwife, who are either a current smoker (self-report or verified through CO reading of ≥ 7 ppm^2^) or ex-smoker (quit within two weeks prior to booking appointment). The exclusion criteria are pregnant women who are not smokers or who have reduced mental capacity.

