### Economic evaluation

A health economic analysis will be undertaken using a cost-consequences analysis approach. Over a period of 12-months, cost data will be collected on wages, travel, training, NRT prescribing and average length of intervention per client. Summary information for these costs will be presented in a tabular format against the consequences of each intervention. Consequences are defined as the primary and secondary outcome measures previously described.

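### Birth outcomes and smoking at birth or third trimester should be limited to women referred before delivery, and 52-week smoking status needs a starting point and a data source that a 12-month study can supply

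*Protocol article*

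**What the plan says.** Two parts of the protocol article's Methods have to be read together.

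**Who enters.** The Sample section states: "The inclusion criteria are pregnant or postnatal women, under the care of a midwife". The Interventions section names the first antenatal appointment and later scheduled antenatal visits as the main referral points, and also allows referral after the birth while a midwife is still responsible for the woman.

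**What is measured, and when.** The Outcome measures section lists "smoking status at the time of birth or third trimester and 52 weeks" and "birth outcomes (low birth weight (<2500 g), preterm birth <37 weeks" among the secondary outcomes. Neither is restricted by time of referral, and the 52 weeks has no stated origin. On duration, the Abstract says "This study will adopt a quasi-experimental design over a 12 month period", and the Interventions section says "The study will take place over 12 months using an integrated approach". The article does not separate a recruitment period from follow-up and gives no closing date for data extraction. Birth outcomes are to come from routine maternity systems, and referral and treatment data from the Stop Smoking Service database (Quantitative data collection).

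**The concern.** There are two separate problems.

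The first is one of time order. A woman referred after delivery has already had her third trimester and her birth. Her baby's weight, the gestation at delivery and her smoking at birth cannot be results of a service she had not yet been offered. Followed as written, the plan counts her in the comparison of those outcomes. A woman who enters postnatally as a current smoker is also likely to have been smoking at birth, so she is selected on something close to the outcome itself. If the proportion of such women differs between intervention and usual care sites, the comparison is distorted as well as diluted. Adjusting for baseline characteristics does not help, because these women have no effect to estimate.

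The second is one of calendar time. A 52-week outcome does not fit inside a 12-month study with staggered entry, and women referred early in pregnancy but late in the year deliver after it ends. If data closed at 12 months, the 52-week outcome would be empty and the birth outcomes would be incomplete.

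**Working it through.** **The plan's own figure.** The only calculated figure is 146 per group per Health Board (Sample size: 10% versus 25%, 5% type I error, 90% power). With a mean proportion of 0.175 and a two-sided test:

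- Without continuity correction: n = [1.960 × √(2 × 0.175 × 0.825) + 1.282 × √(0.09 + 0.1875)]² / 0.15² = 132.8, so 133.
- With continuity correction: (132.8 / 4) × [1 + √(1 + 4 / (132.8 × 0.15))]² = 145.8, so 146.

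The figure reproduces. It concerns engagement only, so the sample size is not in question here.

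**Postnatal entrants.** Let d be the true effect on a birth outcome in women referred antenatally. Let p₁ and p₀ be the postnatal shares in the intervention and usual care groups, r the usual-care risk in antenatal referrals, and s the risk in postnatal referrals, which the service cannot alter. The expected difference in the analysis as written is

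(1 − p₁)(r + d) + p₁s − [(1 − p₀)r + p₀s] = (1 − p₁)d + (p₁ − p₀)(s − r).

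The first term is the diluted effect. The second is a spurious difference, which appears when the postnatal shares differ between groups and the two kinds of women differ in risk. With p₁ = p₀ = 0 the expression is simply d. The article gives neither share, so neither term can be given a size.

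**52 weeks.** Suppose entry is uniform over R weeks and data close F weeks after week 52.

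- The share reaching 52 weeks after entry is F/R, up to a maximum of 1. With F = 0 this is 0%. With R = 52, full capture needs F = 52, that is, data to week 104.
- If the 52 weeks runs from birth, no woman referred antenatally reaches it within the period. For referral at 12 to 8 weeks, the last such date is week 132 to 136.

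**Births.** With referral at gestational week g and delivery at 40 weeks (both assumed; the article gives no gestation at referral), the share delivering by week 52 is (52 − (40 − g)) / R. For R = 52:

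| g (weeks) | Delivered within 52 weeks | Delivered after |
|---|---|---|
| 8 | 20/52 = 38% | 62% |
| 10 | 22/52 = 42% | 58% |
| 12 | 24/52 = 46% | 54% |
| 14 | 26/52 = 50% | 50% |
| 20 | 32/52 = 62% | 38% |
| 28 | 40/52 = 77% | 23% |

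For shorter entry, take the least favourable case, g = 8. With R = 39, 1 − 20/39 = 49% deliver after the period. With R = 26, 1 − 20/26 = 23%.

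**When the last birth occurs.** For entry up to week 52, it is week 52 + (40 − g): week 84 for g = 8 and week 80 for g = 12. That is 28 to 32 weeks after the 12 months, or about 7 months.

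**The case against.** The strongest reply is that the 12 months may describe how long the service is delivered, not when data collection closes. It stands under Interventions and in the abstract, and routine maternity records can be extracted later. The data items are in Additional file 1 and the article refers to an agreed analysis plan. Neither is shown, and a condensed article commonly leaves out an extraction date. This largely stands for births: they can be captured, and the remaining request is to say when. It also means that 52-week status is unobservable within the period, not that it will never be observed. It does not answer the missing starting point, nor the postnatal entrants, because later extraction does not change the order of events.

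A second reply is that postnatal first referral may be rare, since referral is opt-out from the first antenatal appointment and women in intervention sites are asked about smoking at every later one. That is fair and limits the likely size of the problem.

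Four stronger readings are tempting, and the documents do not support them:

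- **That most births fall after the study.** This needs entry throughout the year, referral before about 14 weeks and data closing at week 52. The article fixes none of these, and it names later antenatal visits as a main referral point. Smoking may also be taken in the third trimester. If that starts at week 28 (assumed), (52 − 18)/52 = 65% to (52 − 16)/52 = 69% of women referred at 10 to 12 weeks reach it within the year.
- **That the 52-week comparison is confined to women who engaged.** The article does not say so. It would be an inference from silence while the list of data items is not shown. It is a risk to exclude, not a stated feature.
- **That 12 months of cost data cannot be set beside later outcomes.** The costs listed are mainly those of delivering the service, and a cost-consequences table may show them next to later consequences. Matching the windows is a preference.
- **That missing 52-week status can safely be counted as smoking.** If recording depends on engagement, this creates an effect. With true abstinence of 20% in both groups (assumed) and engagement of 25% versus 10%, recorded abstinence is 0.25 × 20% = 5% versus 0.10 × 20% = 2%. The odds ratio is (0.05/0.95)/(0.02/0.98), about 2.6, with no true difference.

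**Conclusion.** The point holds in two parts, both confined to secondary outcomes.

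The postnatal part rests on the text alone. Women first referred after delivery are eligible, and outcomes settled before their entry are listed without restriction. The effect of the service on those outcomes in those women is zero by construction. How far this dilutes or distorts the comparison cannot be stated, because their share is not given; it may be small.

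The timing part also holds, with limits. Essentially no woman reaches 52 weeks after entry inside a 12-month study with staggered entry, and the origin of the 52 weeks is undefined. The share of births falling after the period is uncertain: about a quarter to 60% under uniform full-year entry, 40-week pregnancies and referral at 28 to 8 weeks, and less with shorter entry. Later extraction would recover them.

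The primary outcome, engagement, and its sample size are unaffected.

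**What to change.** 1. Analyse low birth weight, preterm birth and smoking at birth or third trimester only in women identified as smokers and referred before delivery, with the same rule in both arms. The cost is a filter on referral date and a slightly smaller denominator.
2. State the last entry date and the event from which the 52 weeks is counted. This costs a sentence.
3. Extract the routine maternity data after the last antenatally referred woman has delivered. If entry runs the full year, the final report of these secondary outcomes comes about 7 months later.
4. For 52-week smoking status, choose one of two courses. Either extract it at least 52 weeks after last entry (about 12 months later, and longer if counted from birth) from a source that covers engagers and non-engagers alike, or drop it as a between-group outcome. Do not count unrecorded women as smoking if recording depends on engagement.

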### Sample size

We hypothesise that the flexible models of service delivery can increase the percentage of pregnant women who engage with smoking cessation services from 10 per cent (current rate of engagement in NHS England smoking cessation services) to 25 per cent. A sample size of 146 pregnant smokers in each group within each Health Board will allow a 15 per cent difference to be detected in the proportion of pregnant smokers who engage, with a five per cent type I error rate and 90 per cent power.

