### Quantitative data collection

Quantitative data collection will principally utilise routine data from: i) the Health Board’s electronic Patient Administration System (PAS) and Maternity Information System, which contain information about expectant mothers smoking status and birth outcomes and ii) the NHS Stop Smoking Service database which will record referral and treatment information for all intervention and usual care clients. Each Health Board uses a national standardised maternity record. The maternity record aims to improve quality and safety of maternity care and is updated regularly according to national guidelines to represent the latest recommendations for best practice. Within the record, there is a comprehensive risk assessment which identifies individual risk factors, including smoking status, for the expectant mother. Data from the patient hand-held record is entered into each Health Board’s electronic PAS and Maternity Information System (where available). Additional file 1 provides detail about the specific data items to be extracted from the PAS and Maternity Information System for this study.

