### Analysis

Baseline demographic and social characteristics of pregnant smokers in both intervention and usual care sites will be summarised using descriptive statistics. Comparisons between the two groups will be carried out using a Student’s *t*-test or a non-parametric test for continuous data and a chi-squared test or a Fisher’s exact test for categorical data. Characteristics of women who do not opt out of the referral will be compared to those who do. Continuous data will be expressed as mean values with standard deviations and categorical data will be presented as counts with percentages. A single logistic regression model will be developed to obtain odds ratios for the comparison of different interventions with usual care, and for comparisons between interventions. Differences in baseline characteristics of individuals and referral rates for Stop Smoking Services will be adjusted for. To account for the geographical clustering of individuals, robust standard errors will be calculated.

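### Birth weight is an outcome only as a <2500 g cut, which keeps less than half of the information under a normal shift; adding weight in grams is a cheap improvement

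*Protocol article*

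**What the plan says.** The Outcome measures section of the protocol article places birth outcomes among the secondary outcomes and defines them by two thresholds: "birth outcomes (low birth weight (<2500 g), preterm birth <37 weeks". No mean birth weight or mean gestational age is named.

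The Analysis section gives one comparative model: "A single logistic regression model will be developed to obtain odds ratios for the comparison of different interventions with usual care". It also covers comparisons between interventions, adjustment for baseline differences and referral rates, and robust standard errors for geographical clustering. Continuous data appear mainly in the descriptive part of the same paragraph, where the treatment is summary only: "Continuous data will be expressed as mean values with standard deviations and categorical data will be presented as counts with percentages".

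On data sources, Quantitative data collection refers to the Health Board systems, "which contain information about expectant mothers smoking status and birth outcomes", and leaves the item list to a supplement that is not shown: "Additional file 1 provides detail about the specific data items to be extracted from the PAS and Maternity Information System for this study".

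The article gives no expected effect, event rate, standard deviation or power for any birth outcome.

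**The concern.** Low birth weight is a yes/no cut of a measured weight, placed in the lower tail of the distribution. There, few women lie near the threshold, and a modest shift in the mean moves few of them across it. Comparing proportions then wastes much of what the weights could say about such a shift.

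The Background gives low birth weight as one of the harms that motivate the work, and the Economic evaluation section counts all secondary outcomes as consequences in its cost-consequences table. Any effect of a service model on birth weight has to pass through engagement and then through quitting, so it is diluted over all women in the group. A wide interval on the odds ratio for <2500 g would tell commissioners little, and a narrower one could be had from the same births.

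**Working it through.** **The plan's own figure.** The only stated sample-size calculation is for engagement: an increase "from 10 per cent (current rate of engagement in NHS England smoking cessation services) to 25 per cent", "with a five per cent type I error rate and 90 per cent power". With mean proportion 0.175 and two-sided 5%:

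n = [1.960·√(2·0.175·0.825) + 1.282·√(0.10·0.90 + 0.25·0.75)]² / 0.15² = 132.8 per group

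With the continuity correction, (n/4)·[1 + √(1 + 4/(0.15·n))]² = 145.8, which rounds up to the stated 146. So 146 reproduces. It concerns the primary outcome only.

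**Inputs for birth weight.** From the protocol: the 2500 g cut, 146 women per group per Health Board, and four Health Boards (4 × 146 = 584 per arm if all are pooled). Assumed, because the protocol gives none: low-birth-weight rates of 5% to 15%, a roughly normal distribution, and an intervention effect that shifts the mean.

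**Information kept by the cut.** With rate p and z the normal quantile at p, the efficiency of the cut relative to the mean is φ(z)² / [p(1 − p)]:

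| Assumed rate p | φ(z) | φ(z)² | p(1 − p) | Kept | Lost |
|---|---|---|---|---|---|
| 5% | 0.1031 | 0.0106 | 0.0475 | 22% | 78% |
| 10% | 0.1755 | 0.0308 | 0.0900 | 34% | 66% |
| 15% | 0.2332 | 0.0544 | 0.1275 | 43% | 57% |
| 20% | 0.2800 | 0.0784 | 0.1600 | 49% | 51% |

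The proportion kept reaches one half at a rate of about 21%. In interval terms, the analysis in grams gives a width, on the same standardised scale, of √0.224 = 0.47, √0.342 = 0.58 and √0.426 = 0.65 times that from the cut at rates of 5%, 10% and 15%.

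**Power, to see what this buys.** For a shift of d SD with n per group, the mean has z = d·√(n/2). The cut has z = (p − p₁)/√{[p(1 − p) + p₁(1 − p₁)]/n}, with p₁ = Φ(z_p − d), where z_p is the normal quantile at p. Two-sided 5%, p = 10%, women treated as independent:

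| Assumed shift | 584 per arm: mean v cut | 146 per group: mean v cut |
|---|---|---|
| 0.02 SD | 6% v 5% | 5% v 5% |
| 0.05 SD | 14% v 8% | 7% v 6% |
| 0.06 SD | 18% v 9% | 8% v 6% |
| 0.10 SD | 40% v 16% | 14% v 8% |
| 0.20 SD | 93% v 47% | 40% v 16% |

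To place these shifts: the plan hopes for 25% − 10% = 15 percentage points more engagement. If every extra engager quit and quitting were worth 0.4 SD of birth weight (both assumed), the shift would be 0.15 × 0.4 = 0.06 SD. If one third quit, it would be 0.02 SD. Allowing for clustering lowers the power of both analyses.

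**Does it carry over to preterm birth?** An illustrative left-skewed mixture was used for gestational age (all values assumed): 91% normal with mean 39.5 and SD 1.3 weeks, and 9% with mean 34 and SD 2.5 weeks. This gives an overall SD of 2.14 weeks and 10.44% preterm.

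- Pure shift of 0.1 week: preterm falls to 9.96%. Relative efficiency of the cut = (0.0048²/0.0935)/(0.1²/2.14²) ≈ 0.11.
- Early-birth share falls from 9% to 7%: the mean rises by 0.11 week and preterm falls to 8.73%. Relative efficiency = (0.01715²/0.0935)/(0.11²/2.14²) ≈ 1.19.

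So for gestation the answer depends on where the effect lies, and in the second case the cut loses nothing.

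**The case against.** The strongest reply is that nothing here is an error. Both thresholds are recognised clinical outcomes, they match the review cited in the Background, they are secondary, and no power is claimed for them. That stands, and it is why this is only an improvement.

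Four stronger readings are tempting, and the document does not support them.

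- **That the loss above one half applies equally to preterm birth.** The formula needs a roughly normal shift. With skewed gestational age the result can be reversed, as the mixture shows, and the Background itself speaks of effects on the risk of preterm birth.
- **That birth outcomes carry the study's smallest expected effects.** Dilution through quitting makes a small effect plausible, but the article states no effect on birth outcomes and ranks none.
- **That the cut would cause a finding of no effect.** At 0.02 to 0.06 SD, power is below 20% with either analysis even when all four Health Boards are pooled. The protocol's sample size is set within each Health Board ("A sample size of 146 pregnant smokers in each group within each Health Board"), and the Analysis section also compares the service models with one another. With 146 per group the gain at 0.05 to 0.06 SD is only 1 to 2 points.
- **That weight in grams will certainly go unanalysed.** The article is condensed and refers to an agreed analysis plan that is not shown. What can be said is that the stated outcome definition and the stated model are both binary.

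It is also fair to say that reducing the cut-offs to descriptive counts would give up clinically meaningful comparisons. The remedy should therefore add to them and not replace them.

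**Conclusion.** The point holds for birth weight, as a cheap improvement. As the article stands, birth weight is an outcome only through the <2500 g cut, and the only comparative model is logistic. Under a roughly normal shift the cut keeps about 22% to 43% of the information at rates of 5% to 15%, equivalent to discarding more than half of the women for this question. The rates, the normality and the shift are assumptions, but the conclusion that more than half is lost holds for any rate below about 21%.

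The practical benefit is mainly a narrower interval, about 0.47 to 0.65 times as wide on a common scale. It is not a reliable gain in detected effects. No corresponding claim is made for preterm birth.

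**What to change.** In Outcome measures, add birth weight in grams as an analysed secondary outcome. In Analysis, add that it will be compared by linear regression with the same covariates and the same allowance for clustering as the logistic model, and reported as an adjusted mean difference with a 95% CI. Keep <2500 g and <37 weeks as analysed secondary outcomes.

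The cost is about one sentence in each section and one further secondary analysis. No new data collection is expected, since a weight is needed to derive the cut. It should be confirmed that weight in grams, and not only a flag, can be extracted from the maternity system, because the item list in Additional file 1 is not shown.
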